### Participants

Participants aged ≥18 years old with septic shock and high endotoxin activity (EAA ≥0.60) are eligible for the study. Written informed consent is obtained from each patient or their substitute decision maker prior to randomization. Septic shock is defined as a documented or suspected infection as indicated by either directed or empiric use of antibiotics and presence of hypotension of at least 2 hours duration requiring ongoing vasopressor support despite a fluid challenge of 30 ml/kg in the previous 24 hours. Subjects must also have at least one additional organ failure as defined by oliguria, thrombocytopenia, or need for mechanical ventilation. There is no requirement for subjects to meet any systemic inflammatory response syndrome criteria. Subjects with end-stage renal disease on dialysis are not eligible. The estimated 28-day mortality in this cohort of patients as per the Surviving Sepsis Campaign (SSC) database estimate is 35%
[24].

Investigators agree to managing patients in line with the SSC guidelines
[25,26]. There are no specific management requirements; however, as indicators of overall adherence to SSC guidelines and good clinical practices, two quality measures are being monitored.

### Study procedures

#### Coordination and randomization

A clinical coordinating center (C4) at Cooper University Hospital, Camden, NJ, USA, has been established to confirm subject eligibility for the study and provide support to investigators and study personnel throughout the study period. The C4 consists of four members to evaluate eligibility (sepsis members) and two nephrologists (nephrology members) who provide treatment-related support. Subjects approved for randomization based on meeting full eligibility criteria including an EAA ≥0.60 will be randomized. Randomization will be 1:1 using random block sizes of two and four. Research pharmacists will dispense identical boxes containing either treatment cartridge boxes or sham boxes based on a serial number code linked to the randomization scheme. The sepsis C4 members are blinded to treatment allocation while the nephrology C4 team can be unblinded as needed.

#### Timing

To be eligible for treatment, following a minimum fluid challenge, patients must be in septic shock and on vasopressors at the specified dose levels in Table 
2 for at least 2 hours continuously and not for more than 30 hours. A sample timeline for consent, measurement of EAA, and randomization are shown in Figure 
2. The first treatment must be initiated within 24 hours of the EAA consent and the second approximately 22 hours after the first treatment. A sample timeline for the intervention period is shown in Figure 
3.

**Figure 2 F2:**
[figure not shown]
**Timing for patient identification and enrollment.** EAA, endotoxin activity assay.

**Figure 3 F3:**
[figure not shown]
**Timeline for initiation of intervention.** EAA, endotoxin activity assay.

#### Measurement of endotoxin activity assay

The EAA received 510(k) *de novo* clearance from the FDA in 2003 for the measurement of clinical samples for endotoxemia and to assess patients for risk of severe sepsis. The assay is semi-quantitative and values are expressed as EAA units between 0 and 1. A low EAA level is considered to be <0.40, intermediate level 0.40 to 0.59, and high level ≥0.60 (Spectral Diagnostics Inc., Toronto, Ontario, Canada). These cutoffs were established based on the results of the MEDIC trial
[5]. The details of how to perform the assay are published elsewhere
[27]. In the current trial, samples are run in duplicate by trained personnel. A correlation value of 15% or better is required for EAA results less than <0.20, and 20% for all other EAA results. If a patient is otherwise eligible but the EAA is below the high threshold of 0.60, a follow-up test may be done once, 4 to 6 hours after the first test, to reassess for potential eligibility.

#### Description of the study intervention

Patients assigned to the treatment arm who do not already have access for dialysis will have a standard hemodialysis catheter inserted in one of the femoral veins by an unblinded physician not involved in the clinical care of the patient. For those patients not assigned to the treatment arm, a “cut” hemodialysis catheter and associated dressing will be affixed to the skin in the femoral position to simulate a newly inserted line. The same physician that would have inserted the catheter stays in the room behind a curtain for a similar amount of time as would have been predicted for catheter insertion. At the conclusion of each hemoperfusion session, a standard opaque dressing will be placed over the line site to maintain the blind. After the second hemoperfusion session, the hemodialysis catheter is removed and a standard opaque dressing applied over the region. In some patients the decision for dialysis has been made contemporaneously with the consent for study and in that case a dialysis catheter will be inserted and the treatment blinded only.

The PMX hemoperfusion column used in the study was developed in Japan and is manufactured by Toray Industries (Tokyo, Japan). The PMX treatment will be administered twice using two cartridges with the treatments completed approximately 24 hours apart. Each treatment will last for approximately 2 hours, at a blood flow rate of approximately 100 ml/minute through the circuit (range of 80 to 120 ml/minute). For the current trial, a standard intermittent hemodialysis machine will be used as a blood pump to administer the treatment. At the discretion of the unblinded nephrologist on the hemoperfusion team, anticoagulation, using intravenous unfractionated heparin, will be administered to maintain patency of the circuit for the duration of each 2-hour treatment. Patients already on anticoagulation for other indications or those with coagulopathy will not be anticoagulated further at the discretion of the nephrologist on the hemoperfusion team. Citrate anticoagulation is not allowed as per the recommendations of the manufacturer.

#### Blinding

The trial is blinded. For those patients assigned to the control arm, a simulated or “sham” hemoperfusion event is carried out to coincide with the timing of the treatment events in the other arm. In addition, a “cut” line is placed on the skin to simulate the presence of an indwelling central line. To maintain the trial’s blind, the ICU physician investigators, those health-care professionals involved in recording blinded data, and those who are involved in data analysis, will remain blinded to allocation of treatment.

A nephrology staff member, the study coordinator, the ICU bedside nurse, and a pharmacist will know the treatment allocation and are trained to record allocation and treatment records (timing of device use) and concomitant anti-coagulant medication administered (for example, heparin) on the source documents and case report forms (CRFs) that will be kept blinded from the remaining study personnel.

Nephrology staff will be trained to use the PMX cartridge on those subjects randomized to the treatment arm and to maintain the blind for the subjects that are randomized to the control arm by performing the “sham” perfusion event. Study staff (principal investigator and other ICU personnel involved in the subjects care) and the subject (and/or the subjects surrogate) will remain blinded to the study allocation. Pre-treatment EAA results will be made available to the treating physician, but all subsequent EAA results are blinded. During the period of time of the treatment intervention or sham perfusion event sites employ a number of methods to ensure the blind is maintained. During the treatment phase, a façade perfusion event is conducted whereby a dialysis instrument is brought to the patient’s bedside and curtains are drawn. A sign is attached to the curtain indicating that a study procedure is in progress. The unblinded nephrology team and/or study coordinator perform the hemoperfusion or sham perfusion for approximately 2 hours. This process is repeated once at approximately 22 hours such that the treatment of PMX or sham treatment is completed twice within a 24-hour period.

Breaks in the blind are reported to the sponsor via the medical monitor and are recorded in CRFs. Emergency unblinding procedures include confirmatory correspondence with the pharmacy of the true treatment allocation.

#### Sample size and power

The power analysis is based on a two-sided Fisher’s exact test to compare the proportions of death within or at 28 days between the PMX treatment and control groups. It is assumed that for the control arm of standard medical care alone approximately 35% subjects will die by day 28 after the enrollment. It is also hypothesized that there will be an approximately 15% improvement in 28-day mortality rate for subjects randomized who receive the standard medical care plus the PMX cartridge, as compared to those receiving the standard medical care alone. The overall significance level for the entire sequence of primary efficacy tests is assumed at 5% in a two-sided test. An interim analysis based upon safety only was conducted after 76 patients were enrolled in January 2013. No efficacy analysis was conducted. The data safety monitoring board (DSMB) noted no specific safety concerns at that time. There is one planned additional interim analysis approximately at the midpoint (that is, 180 subjects enrolled). Because of the planned interim analysis, the maximum sample size for the trial (that is, if the trial is not terminated by the interim analysis) is based on the final efficacy test to compare day 28 mortality rate between the two study arms at a significance level of 0.048 based on the method of O’Brien and Fleming
[28].

Assuming a sample size ratio of 1:1 between the two study arms, a sample of 180 subjects per study arm (that is, a total of 360 subjects for both arms) provides at least 80% statistical power to detect the hypothesized effect size (that is, 15% difference) from the final primary efficacy test. The statistical power with the proposed sample size will thus be more than 80% from the entire sequence of the planned primary efficacy analyses. These power analyses assume a 15% attrition rate from the randomized subjects of each study arm. Therefore, a minimum of 306 evaluable subjects are necessary to achieve at least 80% statistical power based on the hypothesized effect size.

#### Monitoring

The trial is fully monitored by the contract research organization responsible for trial operations. A trial monitoring plan has been established and is on file with the FDA. One hundred percent source data verification is done for all data points in the CRFs. Protocol violations are predefined. Adherence to treatment as defined by number of treatments delivered versus prescribed as well as total time of each delivered treatment is compiled in the CRF and tabulated for analysis. All co-interventions are captured including concurrent medications. A detailed policy on co-enrollment in other studies has also been developed and approved by the DSMB.

#### Interim analysis

An interim analysis will be performed by an unblinded statistician independent of the DSMB and the Sponsor after the first 180 subjects (that is, about 90 per study arm, or about 50% of the total planned evaluable subjects) complete their day 28 assessment. The interim analysis will only analyze the portion of the data through day 28 for subjects who have completed the day 28 assessment and is based on the final efficacy test to compare day 28 mortality rate between the two study arms at a significance level of 0.048.

The primary purpose of the interim analysis is to determine if the trial should be terminated early or the study protocol should be modified. The primary population for this interim analysis will be the intention to treat (ITT) population. Secondary analyses will examine the modified ITT population - that is, all patients who have at least one treatment application. The issues to be addressed by the interim analysis will include the possibility that: (a) the treatment is clearly effective so that it is unnecessary to continue to the planned termination point insofar as the primary efficacy endpoint is concerned, *P* value is less than 0.005; or (b) the treatment is so ineffective that continuation of the study would provide little or no chance of ever reaching statistical significance. In addition to the efficacy assessment, at the interim analysis the DSMB will review all serious adverse events and unanticipated serious device effects to evaluate if there are medically significant justifications due to excessive side effects or safety concerns to demand an early end to the trial or a modification of the intervention. The interim analysis will thus evaluate both safety and efficacy variables.

If the trial is not terminated based on the interim analysis, the results of the interim efficacy analysis may be used to revise sample size estimations, which will serve in planning the remaining part of the trial. An independent statistician will conduct the power analyses and sample size re-estimation.

If the trial is terminated as a result of the interim analysis (that is, *P* value < 0.005) or by the recommendations of the DSMB, the final efficacy and safety analyses will be performed using the entire data of follow-up to 12 months or until the last assessment for all subjects randomized prior to the study termination date.

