### Statistical analysis of results

Primary efficacy analyses will be conducted on the ITT population. The primary efficacy endpoint is the all-cause mortality rate of the subjects within 28 days after the initiation of the treatment perfusion or the sham perfusion. Let *P*_0_ and *P*_1_ be the proportion of death within 28 days for the arm of standard medical care alone and the arm of standard medical care plus the PMX cartridge, respectively. The primary efficacy analyses will test the null hypothesis of *H*_0_ : *P*_1_ = *P*_0_ against the two-sided alternative hypothesis of *H*_
*a*
_ : *P*_1_ ≠ *P*_0_. The test of these hypotheses will be carried out through Fisher’s exact test
[29]. A two sided 5% significance level will be assumed for the primary efficacy test. Similar analyses on the primary efficacy endpoint will also be conducted on the per protocol population.

In addition, a long-term follow-up of survival status at 90 days, 6 months and 12 months will be undertaken for the ITT population. This will entail a comparison of survival rates for ITT subjects at 90 days, 6 months and 12 months after assignment to either the treatment perfusion or the sham control perfusion group.

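### The interim modified ITT set is defined by treatment delivery, which is a real extracorporeal procedure in one arm and a facade in the other, so randomisation does not protect that secondary mortality comparison

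*Protocol article*

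**What the plan says.** Under Interim analysis, the protocol article makes ITT primary: "The primary population for this interim analysis will be the intention to treat (ITT) population". It then adds a second set, for secondary analyses: the "modified ITT population - that is, all patients who have at least one treatment application". The same section says that the interim is to determine whether the trial should end early or its protocol be changed. It gives a P value below 0.005 as the efficacy stopping criterion and allows the interim efficacy results to inform a new sample size.

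Under Statistical analysis of results, the final analysis is also by ITT ("Primary efficacy analyses will be conducted on the ITT population"), with a further set alongside it: "Similar analyses on the primary efficacy endpoint will also be conducted on the per protocol population". The article does not define the per-protocol set.

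Description of the study intervention shows what an application involves. A PMX patient without existing dialysis access "will have a standard hemodialysis catheter inserted in one of the femoral veins by an unblinded physician", followed by about 2 hours of blood flow through the circuit at roughly 100 ml/minute. A control receives a cut catheter, and it and the "associated dressing will be affixed to the skin in the femoral position to simulate a newly inserted line". The Blinding section describes the control session as a simulated event behind drawn curtains. The Discussion explains that a true sham perfusion was rejected as invasive and unethical.

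**The concern.** Membership of the modified ITT set depends on something that happens after randomisation and means different things in the two arms. Failed vascular access, a circuit that cannot be started, or a decision that the patient is too unstable for the procedure can remove a PMX patient from the set. None of these need remove an equally ill control. The staff who deliver the session know the allocation, so a decision not to proceed can also depend on the arm. Under Timing, the first session may start up to 24 hours after consent for the endotoxin assay, which leaves time for patients to deteriorate.

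If the PMX patients lost in this way are sicker than average, the remaining PMX group looks healthier than the controls even if the device does nothing. At stake is a mortality comparison presented at an interim that may alter the trial. Beside a neutral ITT result, it could suggest a benefit among patients who were actually treated.

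**Working it through.** **Inputs from the article.** Control 28-day mortality is 35%, final significance level 0.048, and the test is a two-sided Fisher's exact test (Sample size and power). The interim takes place after 180 subjects, about 90 per arm, with a stopping threshold of 0.005 (Interim analysis).

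**Check of the plan's own figures.** For 35% versus 20% at two-sided 0.048 and 80% power, the continuity-corrected formula gives 153 per arm. Then 153/(1 - 0.15) = 180 per arm, or 360 in total, of whom 306 are evaluable. Exact Fisher power at 153 per arm is 80.5%. The stated design is reproduced, and this point disputes none of its numbers. The 15% attrition is assumed equal in the two arms.

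**Assumed inputs.** The article gives no rate of non-delivery and no mortality for untreated patients. Let u be the share of the PMX arm that never receives an application and q their 28-day mortality. First take no such loss among controls and no treatment effect, so that true mortality is 35% in both arms.

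**Formulas.** Mortality in the PMX modified ITT set = (0.35 - u × q)/(1 - u). Spurious gain = 0.35 minus that value = u × (q - 0.35)/(1 - u).

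The false-benefit rate is the exact probability that Fisher's test is significant in favour of PMX, with 90 controls against 90 × (1 - u) PMX patients, rounded to 86 for u = 5% and 81 for u = 10%.

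| u | q | PMX mortality in the set | Spurious gain (points) | False benefit at 0.048 | False benefit at 0.005 |
|---|---|---|---|---|---|
| 0 | - | 35.0% | 0 | 1.7% | 0.15% |
| 5% | 60% | (0.35 - 0.03)/0.95 = 33.7% | 1.3 | 3.0% | 0.3% |
| 5% | 80% | (0.35 - 0.04)/0.95 = 32.6% | 2.4 | 4.0% | 0.5% |
| 10% | 60% | (0.35 - 0.06)/0.90 = 32.2% | 2.8 | 4.5% | 0.6% |
| 10% | 80% | (0.35 - 0.08)/0.90 = 30.0% | 5.0 | 8.3% | 1.4% |

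**Sensitivity of direction and size.**
- With q = 35%, the gain is 0 for any u.
- With u = 10% and q = 20%, PMX mortality is (0.35 - 0.02)/0.90 = 36.7%, a bias of 1.7 points against PMX.
- With u = 2% and q = 80%, the gain is only 0.9 points.
- If controls lose half as many similar patients (5% against 10%, q = 80%), control mortality is (0.35 - 0.04)/0.95 = 32.6% and the gain falls from 5.0 to 2.6 points.
- If both arms lose the same share of the same kind of patient, the gain is 0 for every u and q.

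**The case against.** The strongest reply is that nothing confirmatory is touched. ITT is primary at both the interim and the final analysis, and modified ITT is named once, as a secondary analysis at the interim. That stands, and it limits the importance of the point. A reader might infer that the modified ITT result led to the resizing to 650 patients and the added organ dysfunction exclusion reported under Trial status. The article ties neither change, nor the 0.005 rule, nor the futility judgement to modified ITT.

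Second, the asymmetry has limits. Patients who cannot hold a mean arterial pressure of at least 65 mmHg are excluded at entry. Those with coagulopathy are not barred from the procedure, because the article makes anticoagulation discretionary. One application does not require a completed 2-hour session. Patients with dialysis access, or about to receive it for dialysis, do not differ by arm in catheter placement. A control who dies, withdraws or misses the window receives no sham either. All of this reduces the likely share of arm-specific losses, but does not make delivery equally feasible in the two arms.

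Third, it is tempting to say that the set favours PMX outright. The documents do not show that untreated PMX patients die more often than average, or that they outnumber comparable control exclusions. It is plausible in shock, but it remains an assumption.

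Fourth, a reader might extend the point to the per-protocol analysis as though it too were known to depend on delivery. The article tabulates sessions delivered against prescribed and says that violations are predefined, but it does not define the per-protocol set. A condensed article may leave that definition to the full protocol or the analysis plan.

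**Conclusion.** The point holds in a limited form. The stated modified ITT rule selects on delivery, delivery differs between the arms by design, and that secondary interim comparison is therefore not protected by randomisation. The direction is conditional: towards PMX if never-treated PMX patients have mortality above 35%, none at 35%, and against PMX below it.

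Under assumed PMX-only non-delivery of 5-10% with 60-80% mortality among the untreated, the distortion is 1.3-5.0 points against a design effect of 15 points. The false-benefit rate at the interim size is 3.0-8.3% at 0.048 and 0.3-1.4% at 0.005.

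Larger error rates can be obtained by putting 325 per arm into the calculation: 9.8-24.3% at 0.048 for 10% non-delivery. The article does not plan a modified ITT analysis at that size, so those rates do not describe what it plans. The ITT analyses are not affected by this selection.

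**What to change.** Define modified ITT by a status judged in the same way in both arms: randomised, alive and still eligible at the scheduled start of the first session, whether or not the session was delivered. Analyse every such patient as randomised. Report non-delivery by arm, with reasons and 28-day outcomes; under Monitoring, the article already records sessions delivered against prescribed. State that the modified ITT analysis is supportive and has no role in the stopping or sample-size decision.

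If the per-protocol set is also based on sessions delivered, label it supportive in the same way. Add, rather than substitute, a complier-average estimate with randomisation as the instrument for the effect of receiving PMX.

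Trial status says that the second interim has already taken place. The change therefore bears on how its modified ITT result is described and on any later use of that set.

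The cost is the wording of one or two population definitions, one table and, where it applies, one extra analysis. The secondary estimates may become somewhat less favourable and wider.

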### Statistical analysis of results

Primary efficacy analyses will be conducted on the ITT population. The primary efficacy endpoint is the all-cause mortality rate of the subjects within 28 days after the initiation of the treatment perfusion or the sham perfusion. Let *P*_0_ and *P*_1_ be the proportion of death within 28 days for the arm of standard medical care alone and the arm of standard medical care plus the PMX cartridge, respectively. The primary efficacy analyses will test the null hypothesis of *H*_0_ : *P*_1_ = *P*_0_ against the two-sided alternative hypothesis of *H*_
*a*
_ : *P*_1_ ≠ *P*_0_. The test of these hypotheses will be carried out through Fisher’s exact test
[29]. A two sided 5% significance level will be assumed for the primary efficacy test. Similar analyses on the primary efficacy endpoint will also be conducted on the per protocol population.

In addition, a long-term follow-up of survival status at 90 days, 6 months and 12 months will be undertaken for the ITT population. This will entail a comparison of survival rates for ITT subjects at 90 days, 6 months and 12 months after assignment to either the treatment perfusion or the sham control perfusion group.

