a. Requirement for positive pressure ventilation via an endotracheal tube or tracheostomy tube	10. Subject has severe granulocytopenia (leukocyte count <500 cells/mm^3^) or severe thrombocytopenia (platelet count <30,000 cells/mm^3^)
b. Thrombocytopenia defined as acute onset of platelet count <150,000 μ/L or a reduction of 50% from prior known levels	11. HIV infection in association with a last known or suspected CD4 count of <50/mm^3^
c. Acute oliguria defined as urine output <0.5 ml/kg/hour for at least 6 hours despite adequate fluid resuscitation	12. Subject’s baseline state is non-communicative
	13. Subject has sustained extensive third-degree burns within the past 7 days
	14. Body weight <35 kg
	15. Known hypersensitivity to polymyxin B
	16. Subject has known sensitivity or allergy to heparin or has a history of heparin associated thrombocytopenia
	17. Subject is currently enrolled in an investigational drug or device trial
	18. Subject has been previously enrolled in the current trial
	19. Any other condition, that in the opinion of the investigator, would preclude the subject from being a suitable candidate for enrolment, such as end stage chronic illness with no reasonable expectation of survival to hospital discharge
	20. Multiple Organ Dysfunction Score ≤9 ** - *added post-second interim analysis*

**Table 3 T3:** Cumulative vasopressor index

**Vasopressor**	**Dose Range**	**Dose Range**	**Dose Range**	**Dose Range**
	**1 point**	**2 Points**	**3 Points**	**4 Points**
Dopamine	0 dose ≤ 5	5 < dose ≤ 10	10 < dose ≤ 15	> 15
(mcg/kg/min)				
Epinephrine	-	0 < dose < 0.05	0.05 < dose < 0.1	> 0.1
(mcg/kg/min)				
Norepinephrine	-	0 < dose < 0.05	0.05 < dose < 0.1	> 0.1
(mcg/kg/min)				
Phenylephrine	-	0 < dose < 0.4	0.4 < dose < 0.8	> 0.8
(mcg/kg/min)				
Vasopressin	-	-	-	Any dose
(units/min)				

**Table 4 T4:** Secondary and exploratory outcomes

1.	To compare mortality between the two groups at 90 days, 6 months and 12 months post-start of treatment
2.	To compare the change in endotoxin levels between the PMX cartridge-treated group and the control group at 12 hours after completion of a second PMX cartridge, with a treatment target of ≥15% reduction of EAA levels with PMX cartridge treatment
3.	To compare the changes in vasopressor doses for the two groups from day 0 to day 3
4.	To compare the number of days of need for vasopressors in each group from day 0 to day 28 (days alive and off vasopressors)

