5.	To compare changes in mean arterial blood pressure for the two groups from day 0 to day 3
6.	Comparison of the changes in renal function from day 0 to day 3:
i.	Fluid balance including urine output
ii.	Serum creatinine
7.	To compare the effects of two uses of the PMX cartridge on progression of, and recovery from, organ dysfunction using the multiple organ dysfunction score from day 0 to day 3
8.	To compare the number of days of need for renal replacement therapy in each group from day 0 to day 28 (days alive and off renal replacement therapy)
9.	To compare the number of days of need for mechanical ventilation in each group from day 0 to day 28 (days alive and off mechanical ventilation)
10.	To compare the mean number of days spent in hospital by subjects in each group for survivors to day 28
11.	To compare survival time from baseline to death within 28 days and compare the risk of death between the two study arms
12.	To compare survival time from baseline to death within 90 days and compare the risk of death between the two study arms

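### The 28-day primary endpoint is counted from perfusion start although the analysis is ITT, so randomised patients never perfused have no time zero; time zero also differs between sections

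*Protocol article*

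**What the plan says.** The section Statistical analysis of results names the population first: "Primary efficacy analyses will be conducted on the ITT population". It then defines the primary endpoint as the "all-cause mortality rate of the subjects within 28 days after the initiation of the treatment perfusion or the sham perfusion".

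The Interim analysis section also makes ITT primary. It describes the modified ITT set separately, as "all patients who have at least one treatment application".

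Other places in the article use other origins:

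- Sample size and power, planning assumption: "approximately 35% subjects will die by day 28 after the enrollment".
- Statistical analysis of results, survival at 90 days, 6 months and "12 months after assignment to either the treatment perfusion or the sham control perfusion group".
- Table 4, item 1, the same three time points: "To compare mortality between the two groups at 90 days, 6 months and 12 months post-start of treatment".
- Table 4, item 11: "To compare survival time from baseline to death within 28 days". Item 12 uses the same origin for 90 days. The article does not tie baseline to any of the other origins.

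The Timing section limits the delay: "The first treatment must be initiated within 24 hours of the EAA consent".

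**The concern.** An ITT comparison keeps the balance that randomisation creates only if every randomised patient has a defined outcome on a clock that starts at or before randomisation. Here the clock starts at an event that some patients may not reach.

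The patients are in vasopressor-dependent shock, so a death between randomisation and perfusion is plausible. Such a death does not fall within 28 days after a perfusion that never began. The article does not say whether the patient is then a death, a non-death or not evaluable.

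Failure to start may also depend on the arm. Under Description of the study intervention, PMX patients without dialysis access need a real catheter and then a working circuit. Controls have a cut catheter fixed to the skin. If more PMX patients fail to start and their deaths are not counted, the primary comparison tilts towards PMX. The interim stopping rule at P < 0.005 rests on the same population and endpoint.

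**Working it through.** **1. The stated sample size does not depend on the clock.** The inputs are in Sample size and power: 35% against 20%, two-sided alpha 0.048, 80% power, 1:1 allocation and 15% attrition. The two-proportion formula with continuity correction gives 153 per arm, or 306 in total, and 306 / 0.85 = 360. Both match the article. Exact Fisher power is 0.805 at 153 per arm and 0.869 at 180 per arm. None of these inputs changes with the origin.

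**2. The origins side by side.**

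| Outcome | Place | Time zero |
|---|---|---|
| 28-day mortality, endpoint | Statistical analysis of results | start of perfusion or sham |
| 28-day mortality, planning rate | Sample size and power | enrolment |
| 90-day, 6- and 12-month mortality | Statistical analysis of results | assignment |
| 90-day, 6- and 12-month mortality | Table 4, item 1 | start of treatment |
| Survival time to 28 and 90 days | Table 4, items 11 and 12 | baseline |

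Rows three and four describe the same outcome at the same time points, so both cannot hold. Row two is a rounded planning figure and weaker evidence than the others.

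**3. Patients who start.** The first session must begin within 24 hours of EAA consent, and consent for the assay precedes randomisation. The gap between the randomisation clock and the perfusion clock is therefore under a day in a patient treated to protocol. The Blinding section times the sham event to match treatment. Little bias can arise in this group.

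**4. Patients who never start.** The article gives no non-start rate, so the following are assumptions: 1% to 3% non-start, all non-starters die, true mortality 35% in both arms, no treatment effect. At the revised size of 650 (325 per arm), 325 × 0.01 to 325 × 0.03 is about 3 to 10 patients per arm.

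Let f be the non-start share in an arm.

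- Dropped from the analysis: observed mortality = (0.35 − f) / (1 − f).
- Kept but counted as non-deaths: observed mortality = 0.35 − f.

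| Non-start, PMX vs sham | Dropped | Counted as non-deaths |
|---|---|---|
| equal | 0 | 0 |
| 2% vs 0% | 35.0% − 0.33/0.98 = 35.0% − 33.7% = 1.3 points | 35% − 33% = 2 points |
| 3% vs 1% | 0.34/0.99 − 0.32/0.97 = 34.3% − 33.0% = 1.4 points | 34% − 32% = 2 points |

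The differences favour PMX. A gap of 2 points is the widest that a 1% to 3% range allows.

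**5. Scale.** With 325 per arm, all counted, and alpha 0.048 assumed to carry over, exact Fisher power is 0.767 for a 10-point difference from 35% and 0.848 for 11 points. The trial can thus detect roughly 10 to 11 points with 80% power. With no true effect, the exact rejection rate at 325 per arm is 0.039 for 35% vs 35%. It is 0.052 for 35% vs 33.7% and 0.069 for 35% vs 33%.

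**The case against.** A reader might infer that the perfusion clock turns the ITT analysis into a comparison of treated patients. The article does not support that. No section excludes non-starters or says their deaths go uncounted. ITT is primary at the interim and at the end, and it is set apart from modified ITT. The mortality proportions are defined by arm. After early termination, the final analysis takes in all subjects randomised before the termination date. The natural reading keeps non-starters in, and a full protocol or SAP could give them a fallback day 0.

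A reader might also take the 15% attrition and the 306 evaluable subjects as a sign that non-starters will be removed. The article does not say what that attrition consists of.

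The suggestion that start times differ by arm is also weakened by the text. The sham event is timed to coincide with treatment, and the physician stays behind the curtain for about as long as an insertion would take. Differential failure to start is possible, because only PMX needs a working catheter and circuit, but nothing in the article shows it.

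These points limit the consequence but do not remove the defect. The article states its time origins, and they conflict. Its primary definition, applied as written, has no answer for a randomised patient who is never perfused. That ITT means all randomised patients is itself an inference from the contrast with modified ITT.

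**Conclusion.** The primary endpoint is tied to a post-randomisation event within an ITT analysis. Never-perfused patients have no time zero, and the long-term outcomes have two incompatible origins. This should be fixed, because otherwise the handling of early deaths could be settled after the data are seen.

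The demonstrated effect is small. With 2 points more non-starters on PMX, nearly all dying, 35% mortality and no true effect, the bias towards PMX is about 1.3 points if they are dropped and about 2 points if they are counted as non-deaths. It is zero if non-start is balanced. The non-start rates and the mortality of non-starters are assumptions chosen as a worst case within 1% to 3%. The stated sample size stands.

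**What to change.** Define day 0 as randomisation for 28-day, 90-day, 6-month and 12-month mortality and for both survival-time outcomes. State that ITT means every randomised patient, including those never perfused or sham perfused, and that a death before perfusion counts as a death. Keep the perfusion-start clock only for a sensitivity analysis in the modified ITT set. Align Table 4 items 1, 11 and 12, Sample size and power, and Statistical analysis of results with this definition.

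The cost is one definition in the protocol and the analysis plan. It needs randomisation and death dates; the article does not list them, but a randomised mortality trial must hold them. The figures of 306 and 360 are unchanged. Counting non-starters dilutes the effect slightly. At 180 per arm, if a share of the PMX arm is never perfused and dies at the control rate, exact power goes from 0.869 with no non-starters to 0.862 at 1%, 0.854 at 2% and 0.828 at 5%.
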